### Statistical analyses

The traditional “3 + 3” design remains the prevailing method for conducting phase I cancer clinical trials [32, 33]. It requires no modelling of the dose-toxicity curve beyond the classical assumption for cytotoxic drugs that toxicity increases with dose. This rule-based design proceeds with cohorts of 3 patients. The first 3 patients in the first cohort will be treated at a starting dose that is considered to be safe based on extrapolation. If none experiences a TLD at that dose level, the following 3 patients will be treated at the next higher dose level. The MTD for which no DLT occur will be evaluated according to the CTCAE Version 5.0 (2017) continuously during the study until first follow up (4–6 weeks after surgery) for each cohort and dose level. A DLT is defined as central nerve system necrosis (≥ grade 3) or cerebrospinal fluid leakage (≥ grade 4) or wound infection (≥ grade 4) or wound dehiscence (≥ grade 4) or postoperative hemorrhage (≥ grade 4) or cognitive disturbance (≥ grade 4) or cerebral edema (≥ grade 4) or headache (≥ grade 4) or seizure (≥ grade 4). If no DLT occurs in one dose level, another 3 patients will be treated at the next higher dose level. However, if any of the first 3 patients experiences a DLT, the following 3 patients will be treated at the same dose level. At the highest dose level, at least 6 patients will be treated. Thus, the maximum number of patients enrolled in this study will be 4 × 6 × 3 = 72. Dose will be prescribed to the 80% isodose for linear accelerator (LINAC)-based radiotherapy. The dose escalation continues until at least 2 patients in a cohort of 3–6 patients experience DLTs (i.e., 33% of patients with DLTs at that dose level). The recommended dose for a future phase II trials is conventionally defined as the dose level just below the toxic dose level.

The primary endpoint of this study is safety assessed from the start of radiotherapy until the first follow up after surgery (4–6 weeks after surgery). Based on experience from clinical practice, the number of patients lost to follow-up is expected to be very small. Patients who dropped out of the study between radiation treatment and first follow-up visit will be replaced by a new patient. For patients without a final examination after 1 year, the last valid examination will be used for the assessment of secondary endpoints. All secondary endpoints will be analyzed in an explorative manner using appropriate statistical methods: Mann–Whitney *U* Test (acute toxicity of CTCAE grade 1–3; late toxicity of CTCAE grade 1–5, immunological parameters, time interval between treatment initiation and start of systemic chemotherapy), Fisher’s exact test or Chi-square test (local control rates), log-rank test and Kaplan–Meier curves (OS and PFS at 12-month follow-up), Student *t* test (neurocognitive function), and scaled *t* test (health-related QoL) for independent patients.

The following parameters will be collected and taken into account in analyses applying regression models: age, Karnofsky performance score, extent of neurosurgical resection, recursive partitioning analysis (RPA)-classification.

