**Methods:**

This is a single-center, phase I dose escalation study on neoadjuvant SRS for intracerebral metastases that will be conducted at the Klinikum rechts der Isar Hospital, Technical University of Munich. The rule-based traditional 3 + 3 design for this trial with 3 dose levels and 4 different cohorts depending on lesion size will be applied. The primary endpoint is the MTD for which no dose-limiting toxicities (DLT) occur. The adverse events of each participant will be evaluated according to the Common Terminology Criteria for Adverse Events (CTCAE) version 5.0 continuously during the study until the first follow-up visit (4–6 weeks after surgery). Secondary endpoints include local control rate, survival, immunological tumor characteristics, quality of life (QoL), CTCAE grade of late clinical, neurological, and neurocognitive toxicities. In addition to the intracerebral metastasis which is treated with neoadjuvant SRS and resection up to four additional intracerebral metastases can be treated with definitive SRS. Depending on the occurrence of DLT up to 72 patients will be enrolled. The recruitment phase will last for 24 months.

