### Endpoints

The primary endpoint is the MTD for which no dose-limiting toxicities (DLTs) occur. DLTs will be evaluated according to the Common Terminology Criteria for Adverse Events (CTCAE) version 5.0 (2017) continuously during the study until the first follow-up visit (4–6 weeks after surgery) for each patient and each dose level. Central nerve system necrosis (≥ grade 3), cerebrospinal fluid leakage (≥ grade 4), wound infection ((≥ grade 4), wound dehiscence (≥ grade 4), postoperative hemorrhage (≥ grade 4), cognitive disturbance (≥ grade 4), cerebral edema (≥ grade 4), headache (≥ grade 4), and seizure (≥ grade 4) are defined as DLTs.

Secondary endpoints are as follows:Central nerve system necrosis of CTCAE grade 1–3.Cerebrospinal fluid leakage of CTCAE grade 1–3.Wound infection of CTCAE grade 1–3.Wound dehiscence of CTCAE grade 1–3.Cerebral edema of CTCAE grade 1–3.Local control rates.OS and progression-free survival (PFS) at 12-month follow-up.Time interval between treatment initiation of neoadjuvant SRS and start of systemic chemotherapy.Health-related QoL evaluated using the EuroQoL questionnaire.Neurocognitive function assessed using the Minimal Mental State Examination (MMSE) test.Late toxicity of CTCAE grade 1–5.Immunological and molecular parameters [such as programmed death-ligand 1 (PD-L1) expression, Rapidly Accelerated Fibrosarcoma type B (BRAF) gene mutation, epidermal growth factor receptor (EGRF) mutation, and anaplastic lymphoma kinase [ALK] translocation on the resected specimen].

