#### Dose prescription

Neoadjuvant SRS is applied in a single fraction with single doses depending on the volume and location of the intracerebral metastases requiring neurosurgical resection. The starting dose for the dose escalation scheme will be the dose used by Asher et al. [21] that was already proven to be safe and tolerable in a neoadjuvant setting. The dose will be increased by 2 Gy increments up to the dose recommended by the DEGRO working group on SRS for intracerebral metastases (Table 1) [25]. Doses are prescribed to the 80% isodose line using a linear accelerator.

**Table 1 Tab1:** Cohorts and neoadjuvant SRS dose levels in the present study

Cohort	SRS dose level (Gy)		
	I	II	III
Lesion of ≤ 1.0 cm	18	20	22
Lesion of 1.1–2.5 cm	16	18	20
Lesion of 2.6–3.0 cm	14	16	18
Lesion of 3.1–4.0 cm	12	14	16

The patients will be assigned to 4 different cohorts depending on the largest diameter of the intracerebral metastases to be radiosurgically treated before surgical removal. Each cohort has 3 dose levels. Size and dose were chosen according to the recommondations of the German Society of Radiation Oncology (DEGRO) working group on SRS for intracerebral metastases. The first 3 patients in the first cohort will be treated at a starting dose. If no dose-limiting toxicity (DLT) occurs in that dose level, the following 3 patients will be treated at the next higher dose level; if any of the first 3 patients experiences a DLT, the following 3 patients will be treated at the same dose level. At the highest dose level, at least 6 patients will be treated. Dose will be prescribed to the 80% isodose for linear accelerator (LINAC)-based radiotherapy

*SRS* stereotactic radiosurgery

If further metastases are present (up to 4 in total, no lesion exceeding 4 cm in diameter) that do not require resection, those lesions will be treated with SRS according to the guidelines of the DEGRO working group on SRS for intracerebral metastases [25]. Quantitative analysis of normal tissue effects in the clinic (QUANTEC) reports are applied for dose constraints of normal tissues [26, 27].

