### Sample size calculation

Sample size was determined using the traditional “3 + 3” design as explained below. As radiation dose will differ according to the lesion size, 4 independent cohorts of patients will be evaluated for each lesion size/dose level. With 3 dose levels in 4 different cohorts according to the lesion size, this will lead to a minimal sample size of 4 × [(3 × 3) + 3] = 48 patients, assuming that at least 6 patients should have been tested at MTD in each cohort and that no DLTs occur. In case of DLTs in any patient of a certain dose level group, the size of this group will be enlarged to 6 patients. Therefore, the final sample size might vary.

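### The MTD is defined by zero DLTs but a level is toxic only at two or more, so 1/6 is accepted by one rule and rejected by the other, and at the capped level III nothing settles it

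*Protocol article*

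**What the plan says.** **MTD.** The Endpoints section states: "The primary endpoint is the MTD for which no dose-limiting toxicities (DLTs) occur". The Methods part of the abstract has the same sentence, and Statistical analyses repeats it: "The MTD for which no DLT occur will be evaluated according to the CTCAE Version 5.0 (2017"). Finding the MTD is the primary objective (Objectives).

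**Escalation and phase II dose.** Statistical analyses moves up after 0/3 and adds three patients at the same level after any DLT in the first three. It then sets the stopping point: "The dose escalation continues until at least 2 patients" among three to six at a level have DLTs. It adds: "The recommended dose for a future phase II trials is conventionally defined as the dose level just below the toxic dose level".

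**The ceiling.** Dose prescription says: "The dose will be increased by 2 Gy increments up to the dose recommended by the DEGRO working group". Table 1 gives three levels in each of four lesion-size cohorts. For level III, Statistical analyses says: "At the highest dose level, at least 6 patients will be treated". It does not say how to read the result when fewer than two of those six have a DLT.

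**Patients at the MTD.** Sample size calculation derives its minimum of 48 "assuming that at least 6 patients should have been tested at MTD in each cohort and that no DLTs occur".

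**The concern.** One DLT in six lies between the two rules. It is not zero, so the level cannot be the MTD. It is not two, so the level is not toxic.

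- **Level I or II has 1/6 and the next level is toxic.** The phase II rule recommends the level; the endpoint definition says it is not the MTD.
- **Level III has 1/6.** The endpoint definition rejects level III. The escalation rule has found nothing wrong with it. The phase II rule needs a toxic level, and none exists.

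In the 3.1–4.0 cm cohort, for example, 1/6 at 16 Gy could be reported as an MTD of 16 Gy, as an MTD of 14 Gy or lower, or as no MTD. Each is defensible from the text, and the choice would be made with the data in view.

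A smaller point concerns 0/6 at level III. The endpoint wording and the 48-patient scenario together make this the MTD, although the data show only that no toxic level was met up to a preset dose. In that same scenario the phase II rule yields no dose.

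**Working it through.** **1. The plan's own figures.** Minimum: 4 × [(3 × 3) + 3] = 48. Maximum: 4 × 6 × 3 = 72. Both reproduce. The 48 places the extra three patients of each cohort at the MTD with no DLTs anywhere; that can only be level III with 0/6.

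**2. How far apart the two criteria are.** For six patients at a true DLT rate of 10%:
- at least one DLT (fails the zero-DLT definition): 1 − 0.9⁶ = 0.469
- at least two DLTs (toxic): 1 − 0.9⁶ − 6 × 0.1 × 0.9⁵ = 0.114

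**3. How often 1/6 decides a cohort.** The article gives no DLT rates, so q₁, q₂, q₃ for levels I to III are assumptions, taken as equal and independent across the four cohorts. Rising curves are the main case because Statistical analyses assumes that toxicity increases with dose.

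Rules enumerated: level I or II passes with 0/3, or with 1/3 followed by 0/3. A level is toxic at two or more DLTs. Level III receives six patients unless it is toxic in the first three. After a toxic level, a level below that passed with 0/3 is expanded to six, as Sample size calculation requires at the MTD, and is itself toxic at two or more.

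- Pass(q) = (1−q)³ + 3q(1−q)⁵
- P(1/6 at III) = Pass(q₁) × Pass(q₂) × 6q₃(1−q₃)⁵
- P(0/6 at III) = Pass(q₁) × Pass(q₂) × (1−q₃)⁶
- P(at least one of four cohorts) = 1 − (1−p)⁴

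Example, 5/10/20%: Pass(0.05) = 0.9734 and Pass(0.10) = 0.9061. P(1/6 at III) = 0.9734 × 0.9061 × 0.3932 = 0.347, and 1 − (1 − 0.347)⁴ = 0.82.

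| Assumed rates I/II/III | 1/6 at III | 1/6 at II | 1/6 at I | Total | Total, at least one of four | 0/6 at III |
|---|---|---|---|---|---|---|
| 3/6/10% | 0.338 | 0.030 | 0.006 | 0.373 | 0.85 | 0.51 |
| 5/10/20% | 0.347 | 0.119 | 0.023 | 0.489 | 0.93 | 0.23 |
| 5/15/30% | 0.240 | 0.225 | 0.048 | 0.513 | 0.94 | 0.09 |
| 10/20/30% | 0.194 | 0.207 | 0.114 | 0.515 | 0.94 | 0.08 |

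For level III alone, at least one of four cohorts shows 1/6 with probability 0.81, 0.82, 0.67 and 0.58.

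**4. Sensitivity.**
- Flat 5/10/15/20%: total 0.234, 0.362, 0.415, 0.415 per cohort. Without the expansion from three to six: 0.227, 0.326, 0.338, 0.303.
- Low rates: 1/2/3% gives 0.155 per cohort (at least one of four: 0.49); flat 2% gives 0.11 (0.37); flat 1% gives 0.06 (0.21). Here almost all of the problem sits at level III.

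**5. What six patients show.** One-sided exact 95% upper bounds on the DLT rate:
- 0/6: 1 − 0.05^(1/6) = 39%
- 1/6: 58% (Clopper–Pearson)
- 0/3: 1 − 0.05^(1/3) = 63%

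The 0/6 bound is why a clean level III does not establish an MTD. The 0/3 bound is why six patients at the MTD should stay a requirement.

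**The case against.** The MTD and the recommended phase II dose can be read as two quantities. The sentence on the level below the toxic one never uses the term MTD. A zero-DLT MTD reported beside a separate phase II dose is awkward but possible, and a zero-DLT standard for mostly grade 4 neurosurgical events might be deliberate. The article also names the traditional 3 + 3 design, so a reader may take the zero-DLT wording as loose and apply the usual convention. It condenses a full protocol that may contain a rule for level III.

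The size can be disputed too. DLTs are grade 4 or higher except necrosis (grade 3 or higher) and are counted only to 4–6 weeks after surgery. The starting dose is described as already shown to be safe. The comparative neoadjuvant series in the Discussion report symptomatic necrosis of 4.9% at two years and 5.6%, though mostly at lower doses. Rates of 20% to 30% at level III may therefore be too high.

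Some of this stands. The rates are assumptions and the main curves lean high, so the low-rate results belong beside them. That 0/6 at level III is labelled the MTD is an inference from two places, not an explicit rule.

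The rest does not remove the conflict. If the two quantities are separate, the primary endpoint still contradicts the criterion by which the trial escalates. If the wording is loose, it is loose in all three statements of the primary endpoint. Both rules are printed in the article, so this is a stated contradiction and not a detail left to another document.

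**Conclusion.** The concern holds. As written, 1/6 is tolerated by the escalation rule and excluded by the MTD definition, and at level III no stated rule gives a dose. Under the assumed rising curves this decides 37% to 51% of cohorts. Even at a flat 1%, at least one of four cohorts is affected in about one trial in five. These figures depend on the assumed rates, on equal rates in the four cohorts, and on expanding a 0/3 level to six before it is declared the MTD. The contradiction in the text depends on none of them.

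The 0/6 label at level III is a secondary point. Capping the ladder at the guideline dose is not at fault, and a toxic level I needs no new rule. Patient safety during escalation is unaffected; what is at stake is an unambiguous primary result. The correction should be made before any result is read.

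**What to change.** Replace the zero-DLT definition in Endpoints, Statistical analyses and the abstract:

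1. The MTD is the highest level with at most one DLT in six patients when the next higher level is toxic (two or more DLTs). The rule applies at every level.
2. If level III has at most 1/6, report that the MTD was not reached within the tested range. Name level III as the highest tested and recommended phase II dose. Give its DLT count with the one-sided exact 95% upper bound (39% for 0/6, 58% for 1/6).
3. Keep at least six patients at the MTD. If a level passed with 0/3 and the next is toxic, expand it to six before declaring it. If it then shows two or more DLTs, it is toxic and the rule moves down one level.
4. Treat six patients at level III when it is the highest level reached without being toxic.

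Dose levels, escalation steps and visits do not change. No patients are needed beyond what Sample size calculation already requires; the maximum stays at 18 per cohort and 4 × 18 = 72 in total.

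The cost is one of substance. Accepting 1/6 gives up the stricter stated definition in favour of the criterion the escalation rule already uses. Some cohorts will report that the MTD was not reached, and a recommended dose may carry one observed DLT and an upper bound of 58%.

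### A dose level is filled to six after any DLT in the first three patients, even when two or three DLTs have already shown it to be toxic

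*Protocol article*

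**What the plan says.** The expansion rule appears three times in the protocol article, each time without an upper limit on the number of DLTs:

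- Statistical analyses: "However, if any of the first 3 patients experiences a DLT, the following 3 patients will be treated at the same dose level".
- Dose prescription, note to Table 1: "if any of the first 3 patients experiences a DLT, the following 3 patients will be treated at the same dose level".
- Sample size calculation: "In case of DLTs in any patient of a certain dose level group, the size of this group will be enlarged to 6 patients".

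A separate requirement, in Statistical analyses and in the Table 1 note, concerns level III: "At the highest dose level, at least 6 patients will be treated". It carries no condition on DLTs.

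The toxicity criterion is in Statistical analyses: "The dose escalation continues until at least 2 patients in a cohort of 3–6 patients experience DLTs". The same section then says: "The recommended dose for a future phase II trials is conventionally defined as the dose level just below the toxic dose level". The planned totals are a minimum of 48 (Sample size calculation) and a maximum of 72 (Statistical analyses).

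**The concern.** As written, *any* DLT covers one, two or three DLTs in the first three patients. In a conventional 3 + 3 design only exactly one in three leads to expansion, because only then is the level still undecided. Here a level with two or three DLTs is also filled to six. The criterion sentence says when escalation ends; it does not say that enrolment at the current level stops. The two rules do not strictly contradict each other, but they are badly matched.

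What is at stake is avoidable exposure. Three further patients would receive a single-fraction dose that the plan already classes as toxic. Eight of the nine listed DLT types are grade 4 or worse, and the ninth is central nervous system necrosis of grade 3 or worse. These patients would contribute nothing to the dose decision.

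**Working it through.** **1. The plan's own totals.** Minimum: 4 × [(3 × 3) + 3] = 48. Maximum: 4 × 6 × 3 = 72. Both reproduce exactly.

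**2. Can expansion after two or three DLTs change the decision?**

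- 2 DLTs in the first 3: the total after three more is 2, 3, 4 or 5 of 6.
- 3 DLTs in the first 3: the total is 3, 4, 5 or 6 of 6.

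Every outcome meets the criterion of at least two DLTs in 3–6 patients (the lowest is 2/6 = 33%). The level stays toxic and the recommended dose stays one level below.

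**3. How often would it happen at one level?** For a true DLT rate p, P(≥2 of 3) = 3p²(1 − p) + p³. The share of expansions that cannot matter is P(≥2 of 3) / [1 − (1 − p)³]. The values of p are assumptions.

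| p | P(≥2 of 3) | P(any DLT in 3) | Share of expansions that are futile |
|---|---|---|---|
| 0.10 | 0.028 | 0.271 | 10% |
| 0.20 | 0.104 | 0.488 | 21% |
| 0.30 | 0.216 | 0.657 | 33% |
| 0.40 | 0.352 | 0.784 | 45% |

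**4. Whole trial.** Assume the same rates p₁, p₂, p₃ for levels I–III in all four cohorts. Let Rᵢ be the probability that a cohort reaches level i, with R₁ = 1. If 1/6 permits escalation, Rᵢ₊₁ = Rᵢ × P(0/3) × [1 + P(1/3)]; if it does not, Rᵢ₊₁ = Rᵢ × P(0/3). With S = Σ Rᵢ × P(≥2 of 3 at pᵢ):

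- excess patients per trial = 4 × 3 × S;
- probability that at least one cohort is affected = 1 − (1 − S)⁴;
- additional DLTs = 4 × 3 × Σ Rᵢ × pᵢ × P(≥2 of 3 at pᵢ).

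Worked example, 5/10/15%, with 1/6 escalating:

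- R₂ = 0.8574 × (1 + 0.1354) = 0.9734.
- R₃ = 0.9734 × 0.729 × (1 + 0.243) = 0.8821.
- S = 0.00725 + 0.9734 × 0.028 + 0.8821 × 0.06075 = 0.0881.
- Excess = 12 × 0.0881 = 1.06 patients.
- Trials affected = 1 − 0.9119⁴ = 0.31.
- Additional DLTs = 12 × (0.00725 × 0.05 + 0.02726 × 0.10 + 0.05359 × 0.15) = 0.13.

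Results for all four scenarios:

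| Assumed rates, levels I/II/III | Excess patients, 1/6 escalates | Of which levels I–II | Of which level III | Trials affected | Additional DLTs | Excess patients (trials affected), 1/6 does not escalate |
|---|---|---|---|---|---|---|
| 2/5/10% | 0.43 | 0.10 | 0.33 | 13% | 0.04 | 0.37 (12%) |
| 5/10/15% | 1.06 | 0.41 | 0.64 | 31% | 0.13 | 0.83 (25%) |
| 10/20/33% | 3.43 | 1.47 | 1.96 | 74% | 0.91 | 2.39 (59%) |
| 15/25/40% | 4.32 | 2.26 | 2.06 | 83% | 1.32 | 2.98 (68%) |

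The level III column shows the excess that would remain if only the word *any* were corrected and the six-patient requirement stayed unconditional. Patients 5 and 6 treated after a second DLT in patient 4 or 5 are not counted.

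**The case against.** **Intent.** The design is named as the traditional 3 + 3. The criterion speaks of 3–6 patients, and the lower bound of 3 would have no use if every level with a DLT were filled to six before being judged. The natural combined reading is that 2/3 settles the level. This probably is what was meant. But the sentence governs escalation, and the explicit instruction on enrolment, given three times, says the opposite for 2/3 and 3/3.

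**Level III.** The Sample size calculation section ties the extra three patients to testing six at the MTD when no DLTs occur, and a level with two DLTs is not the MTD. That explains the minimum of 48. It does not condition the top-level sentence in Statistical analyses or the Table 1 note.

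**Size.** The document points towards low DLT rates: the threshold is mostly grade 4, the window closes 4–6 weeks after surgery, the starting dose is described as already safe, and symptomatic necrosis in the cited series was 4.9% and 5.6%. Those series used other doses and margins and do not fix the rate, but the low scenarios deserve weight. At an assumed 1/2/5% the same formulas give 0.10 excess patients, 0.005 additional DLTs and 3% of trials affected. This stands: if toxicity is rare, the practical effect is small.

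**Safeguards and condensation.** A full protocol exists and may hold a decision table. The article nevertheless states the rule itself, so this is not an omission. The DSMB can recommend termination but is only required to review at least twice a year, and nothing links it to a second DLT.

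**Conclusion.** The concern holds. Following the stated rules after two or three DLTs in the first three patients treats three more at a dose that can no longer be found tolerable. That conclusion needs no assumption about DLT rates. The expected size does: from 0.4 patients and 0.04 additional DLTs per trial at 2/5/10% to 4.3 patients and 1.3 DLTs at 15/25/40%, with equal rates in all four cohorts and 1/6 permitting escalation. The effect is largest when the doses prove toxic, which is when the stopping rule is needed. The recommended dose and the planned totals are not affected. It should be fixed, because the harm is avoidable severe toxicity and the repair costs almost nothing.

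**What to change.** State the following in Statistical analyses and the Table 1 note, with point 1 also in Sample size calculation:

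1. A dose level is expanded to six only if exactly one of its first three patients has a DLT.
2. Once two patients at a level have had a DLT, that level is closed to further enrolment at once and declared toxic.
3. The six-patient requirement at the highest level applies only while fewer than two DLTs have occurred there.

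All three are needed: correcting *any* alone leaves level III forced to six, and point 2 also covers a second DLT in patient 4 or 5.

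The cost is wording only. The maximum is still reachable, with one DLT in six at levels I and II and six patients at level III: 4 × (6 + 6 + 6) = 72. The no-DLT minimum is still 4 × (3 + 3 + 6) = 48. The expected number of patients falls slightly.

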### Data collection, management, and analysis

As used in this study, the term Case Report Form (CRF) should be understood to refer to a paper form or an electronic data record or both, depending on the data collection method used in this trial. For this trial, relevant data will be documented in paper-printed CRFs. All findings including clinical and laboratory data will be documented in the subject’s medical record and in the CRF by the investigator or an authorized member of the study team. The investigator is responsible for ensuring that all sections of the CRF are completed correctly and that entries can be verified against source data. In some cases, the CRF, or part of the CRF, may also serve as source documents: Karnofsky Performance Status, Documentation of Clinical-Neurological Examination. In these cases, a document should be available at the investigator’s site and clearly identify those data that will be recorded in the CRF, and for which the CRF will stand as the source document. There is no financial compensation for the participant. In case that the participant discontinues the study, documented medical parameters will not be collected and used for statistical analysis. In case of deviation from intervention protocol, e.g., no SRS prior to resection, the participant is excluded from the study.

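### The drop-out and discontinuation rules make no exception for a patient who already had a DLT, so read literally they can remove an observed DLT from the escalation count

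*Protocol article*

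**What the plan says.** Four places in the protocol article bear on this.

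- **Statistical analyses, replacement:** "Patients who dropped out of the study between radiation treatment and first follow-up visit will be replaced by a new patient". The same paragraph runs the primary safety assessment from the start of radiotherapy to the first post-surgical follow-up, so the replacement interval and the DLT window coincide. It adds that "the number of patients lost to follow-up is expected to be very small" and gives no figure.
- **Data collection, management, and analysis:** "In case that the participant discontinues the study, documented medical parameters will not be collected and used for statistical analysis". A second rule follows: "In case of deviation from intervention protocol, e.g., no SRS prior to resection, the participant is excluded from the study".
- **Endpoints:** DLTs are evaluated "continuously during the study until the first follow-up visit (4–6 weeks after surgery) for each patient and each dose level".
- **Statistical analyses, escalation:** "However, if any of the first 3 patients experiences a DLT, the following 3 patients will be treated at the same dose level". And: "The dose escalation continues until at least 2 patients in a cohort of 3–6 patients experience DLTs".

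The replacement and discontinuation rules are unconditional. The escalation rules do not say whether a DLT still counts if the patient later leaves.

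**The concern.** The primary endpoint rests on very small counts: 0, 1, or at least 2 DLTs among 3 to 6 patients at each of 4 × 3 = 12 cohort and dose-level combinations. Apart from necrosis, which counts from grade 3, every listed DLT is an event of grade 4 or higher. A patient with such an event may plausibly withdraw before the follow-up visit. If that patient is replaced and the data set aside, the DLT leaves both numerator and denominator, and the next decision rests on the replacement. The decision at stake is whether a level is declared toxic, and so which dose the next patients receive and which dose is carried into phase II.

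This is not a detail left for an analysis plan. The article states explicit rules for who counts, and they do not fit its own rule for acting on DLTs.

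**Working it through.** **1. The plan's own figures.** Minimum 4 × [(3 × 3) + 3] = 48 and maximum 4 × 6 × 3 = 72. Both reproduce. Neither includes replaced patients.

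**2. Effect of one removed DLT.** Under the stated rules, 1/3 means three more patients at the same level and 0/3 means escalation; 2/6 means stop and 1/6 means continue. If one DLT patient is removed and the replacement has no DLT, 1/3 becomes 0/3 and 2/6 becomes 1/6. At a true DLT rate of 0.33, a replacement is DLT-free with probability 1 − 0.33 = 0.67.

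**3. Inputs for the average effect.** The article gives no drop-out rate, so all rates here are assumptions.

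- p: true DLT probability. The main case is 0.33, close to the 33% the article attaches to its toxic level.
- dD: probability of leaving after a DLT, taken as 0.10, 0.25 or 0.50.
- dN: probability of leaving without a DLT, taken as 0.02.
- A level passes at 0/3, or at 1/6 after expansion. This follows from escalation continuing until at least 2 DLTs.

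**4. Formulas.**

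- DLT rate among retained patients, rules read literally: q = p(1 − dD) / [p(1 − dD) + (1 − p)(1 − dN)].
- Chance that a level passes: (1 − q)³ + 3q(1 − q)⁵.
- Six-patient top level, at most 1 DLT: (1 − q)⁶ + 6q(1 − q)⁵.

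**5. Results at p = 0.33.** With no departures, q = 0.33 and the pass probability is 0.67³ + 3 × 0.33 × 0.67⁵ = 0.301 + 0.134 = 0.434.

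| dD | q | Level passes | Six-patient top level, ≤ 1 DLT |
|---|---|---|---|
| none (dN = 0) | 0.330 | 0.43 | 0.36 |
| 0.10 | 0.297/(0.297 + 0.6566) = 0.311 | 0.47 | 0.40 |
| 0.25 | 0.2475/(0.2475 + 0.6566) = 0.274 | 0.55 | 0.48 |
| 0.50 | 0.165/(0.165 + 0.6566) = 0.201 | 0.71 | 0.65 |

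**6. Other true rates, same departure assumptions.** At p = 0.20 the pass probability goes from 0.71 to 0.74, 0.79 or 0.88. At p = 0.50 it goes from 0.17 to 0.20, 0.26 or 0.42.

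**7. Direction.** If dD = dN the factor cancels, q = p, and there is no bias. If dN exceeds dD, q exceeds p and the bias is upward. Downward bias needs departure to be likelier after a DLT.

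**8. If observed DLTs always count.** Replacing only DLT-free leavers gives a rate of p / [p + (1 − p)(1 − dN)] = 0.33/(0.33 + 0.6566) = 0.334, whatever dD is. The pass probability is 0.43, against 0.55 (dD = 0.25) or 0.71 (dD = 0.50) under the literal rules.

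**The case against.** - **The article never says a DLT is discarded.** A reader might infer that it does, but this comes only from combining general sentences in two sections. The escalation rule acts once a patient experiences a DLT, with no completion condition, and DLTs are evaluated continuously. On that reading the DLT has already triggered its consequence before the patient leaves. This stands as a possible reading. It shows that the sections conflict; it does not show which one governs.
- **A reader might infer that the bias always favours a higher dose.** The documents do not support that. Compared with the true rate there is none if drop-out is independent of DLT, and no figure in the article shows otherwise.
- **Losses are expected to be few.** This limits the average effect, and at 10% departure after a DLT the shift is only 0.43 to 0.47. It does not protect a decision that a single patient can reverse.
- **Missing a visit is not dropping out.** Fair. Under Assessment of endpoints, patients are also examined on the first postoperative day and at discharge, so a missed later visit need not erase an earlier event.
- **The deviation exclusion gives weak support.** Its only example is a patient without SRS before resection, whose exclusion from a dose-toxicity count is reasonable. The example is not exhaustive, so the limit should be stated, but the rule does not show that irradiated patients with a DLT are excluded.
- **The monitoring board reviews adverse events.** It does so at least twice a year, but nothing under Monitoring puts a DLT back into the count.
- **The full protocol, version 1.1, is not shown** and may define who is evaluable for DLT. That limits certainty about the trial, not about the article's wording.

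**Conclusion.** The point holds as a conflict between stated rules that can produce a wrong escalation decision. Replacement covers exactly the DLT window, discontinued participants' data are not used, and neither rule exempts an observed DLT, while the escalation text acts on any DLT. The firm part needs no drop-out assumption beyond one departure: a single removed DLT, replaced by a DLT-free patient, can reverse a decision at 3 to 6 patients. The average size is conditional. At a true rate of 33% the pass probability rises by about 0.04, 0.12 or 0.27 for assumed departure of 10%, 25% or 50% after a DLT (2% otherwise), and by nothing if departure is unrelated to DLT. The article supports neither a claim that bias is certain nor a claim that it always runs one way.

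**What to change.** Reconcile Data collection, management, and analysis with Statistical analyses by stating that:

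1. A DLT observed in the window, in any patient who received neoadjuvant SRS, counts in the escalation decision whatever happens afterwards (withdrawal, death or deviation).
2. Only patients who leave without a DLT before the window ends are replaced, and each is listed with the reason. Those leaving because of toxicity below DLT grade are reported separately, and their handling is stated in advance.
3. Data collected up to discontinuation are kept for the safety analysis, within the consent given.
4. The deviation exclusion applies to patients who did not receive SRS before resection, not to irradiated patients with a DLT.

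Because the window is tied to surgery, the text should also say how it ends for an irradiated patient who is not operated on.

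The cost is wording only, and the nominal 48 and 72 do not change. Some patients who would have been replaced will count as DLTs, so some levels may expand or stop that would otherwise have passed. The revised rule leans slightly cautious when DLT-free patients leave: with 10% departure in both groups, the rate it uses is 0.33/(0.33 + 0.67 × 0.90) = 0.354 against a true 0.330, and the pass probability is 0.39 against 0.43.
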